
***Treatment-related variables***:Medication useInterventions performed (*i.e.*, type and number of interventions)Sequential Organ Failure Assessment (SOFA) score on day 1 to 4 (or until ICU discharge or death).Length of stay in the ICUMortality during ICU stay and during hospital stay

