### Sample size calculation

In order to reliably calculate correlation coefficients for the association between IAP, I-FABP and Claudin-3 levels, at least 75 patients with IAH are needed. Malbrain *et al.* showed in a multicenter study that in a general ICU population, the prevalence of IAH (*i.e.*, IAP > 12 mmHg) and ACS (*i.e.*, IAP > 20 mmHg with concomitant new organ dysfunction) was 32%, and 4%, respectively [23]. Since we will only follow-up on patients with a minimum of two IAH/ACS risk factors, the percentage of enrolled patients that will develop IAH or ACS will be higher, and is likely to exceed 40% (unpublished data). Therefore, enrolling a total population of 200 patients will be sufficient to ascertain availability of 80 patients with IAH.

This will also be sufficient to compare I-FABP levels in patients with physiologic IAP levels with patients that developed IAH with adequate statistical power. Based upon data provided by Kanda *et al*. we expect that mean I-FABP levels will be 20.0 ± 10.0 ng/mL (range 0–100 ng/mL) in patients without IAH [32]. In patients with IAH, the I-FABP levels will be higher (≥20 ng/mL). An overall population of 200 patients (consisting of 120 controls and 80 patients with IAH) will be sufficient to detect a 0.5 SD increase to 30.0 ± 12.5 ng/mL in I-FABP level in patients with IAH (two-sided test with an α level of 0.05) with >90% statistical power.

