**ASSESSMENTS:**			
**Baseline variables**	X		
**Disease-related variables**	X		
**IAP measurement**		X	
**Blood sample**		X	
**Urine sample**		X	
**I-FABP measurement**		X	
**Claudin-3 measurement**		X	
**Creatinine measurement**		X	
**Treatment-related variables**		X	
**SOFA score**		X	
**Adverse events**		X	X
**Length of ICU stay**		X	X
**Mortality during ICU stay**		X	X
**Secondary interventions**		X	X

*Patients are considered eligible as soon as two IAH risk factors are present. This can either be at ICU admission or later on during ICU stay.

**Patients are followed until 72 hours or until discharge from the ICU, whichever comes first. Measurements are performed every six hours.

Urine samples for measurement of I-FABP, Claudin-3 and creatinine levels: A single fresh specimen of urine will be collected from the urinary bladder catheter that is already in situ. Samples will be kept on ice and then frozen at −80°C in aliquots within two hours of collection.Blood samples for measurement of serum I-FABP levels (NB: this only applies to patients enrolled at Erasmus MC, Rotterdam, the Netherlands): A single blood sample (10 mL) will be drawn from the arterial line that is already *in situ*. Blood will be collected in pre-chilled vacutainer containing EDTA as anticoagulent (BD Vacutainer, Becton Dickinson Diagnostics, Aalst, Belgium) and kept on ice. Blood will be centrifuged at 4°C, 4000× g for 15 minutes. Serum will be stored in aliquots at −80°C within 2 hours until analysis.

The reason for following up on patients during the first 72 hours after enrollment is based upon our observation (unpublished data) that over 95% of patients that deteriorate clinically due to increased IAP will do so during the 12–24 hours. In order not to miss any patients that may deteriorate somewhat later (*e.g.*, due to leak at the surgical site), we have set the time frame at 72 hours.

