In order to assess if levels of I-FABP or Claudine-3 can be used as a prognostic marker for intestinal ischemia-related morbidity it is necessary to also collect clinical data of patients during their entire stay at the ICU. These data will be extracted from the ICU patient data management system (PDMS), where they are stored as part of clinical routine. This will be done using the APACHE II, APACHE IV, SAPS II and SOFA score, which will be collected routinely for any patient admitted to the ICU. Follow-up in the ICU will include a daily physical examination, vital signs monitoring, routine blood tests, and chest radiographs or other ancillary tests as required. The attending physicians will record complications and events as well as any (secondary) intervention performed such as decompression laparotomy.

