### Statistical analysis

Data will be analyzed at the end of the study using the Statistical Package for the Social Sciences (SPSS) version 21 or higher (SPSS, Chicago, Ill., USA) and will be reported following the STrengthening the Reporting of OBservational studies in Epidemiology (STROBE) guidelines. No interim analysis will be done. Normality of continuous data will be assessed by the Shapiro Wilk tests and by inspecting the frequency distributions (histograms). Homogeneity of variances will be tested using the Levene’s test.

Descriptive analysis will be performed in order to report baseline characteristics (intrinsic variables and disease-related variables) and outcome measures of the entire cohort as well as for the group of patients that develop IAH (IAH group; IAP of 12 mmHg or higher on two separate recordings) versus those that do not (control group). For continuous data mean and SD (parametric data) or medians and percentiles (non-parametric data) will be calculated and reported. For categorical data, numbers and frequencies will be calculated and reported for the entire cohort and for the IAH and the control group separately.

Univariate analysis will be performed in order to test the difference in the primary and secondary outcome measures between the IAH group and the control group. Continuous data such as the I-FABP level (primary outcome) of the Claudin-3 level (secondary outcome) will be tested using a Student’s *T*-test (parametric data) or a Mann Whitney *U*-test (non-parametric data). Chi-squared analysis will be used for statistical testing of categorical data such as the number of secondary interventions. A p-value <0.05 will be taken as threshold of statistical significance. Depending upon the number of patients within the cohort of the study that develop ACS and the mortality rate, similar tests will be used to compare data for those who developed ACS (or those who died) versus those who did not. The patient cohort to be included will be heterogeneous by nature, as IAH and ACS risk factors will differ between patients. If it is possible to identify subgroups of patients (*e.g.*, liver transplant patients) subgroup analyses may be performed. P-values <0.05 will be taken as threshold of statistical significance.

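### The number of secondary interventions is classed as categorical and tested by chi-squared; if it is a per-patient count, the rank test already in the plan is the better choice

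*Protocol article*

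**What the plan says.** In the protocol article, Statistical analysis, t-tests or Mann-Whitney tests are assigned to continuous data such as I-FABP and Claudin-3. The next sentence turns to the other kind of data: "Chi-squared analysis will be used for statistical testing of categorical data such as the number of secondary interventions". The threshold follows: "A p-value <0.05 will be taken as threshold of statistical significance". The paragraph then extends the same kinds of test to patients with and without ACS, and to those who died and those who did not.

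Three other places bear on what the variable is:

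- Baseline, disease and treatment-related data lists interventions performed and specifies "type and number of interventions", next to length of ICU stay and mortality.
- Table 1 has a row "Secondary interventions", marked for the measurement period and for close-out, with no unit.
- Study procedures says that the attending physicians record complications and events "as well as any (secondary) intervention performed such as decompression laparotomy".

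No section gives an expected rate, a distribution, an effect size or a power for secondary interventions, or says how a number would be grouped into categories.

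**The concern.** A number of events per patient is an ordered count: two interventions are more than one, and three more than two. Pearson's chi-squared treats the values as unordered labels. If each value is its own category, the comparison is spread over several degrees of freedom, and the high counts give sparse cells. If the count is reduced to any versus none, a patient with three interventions is treated like a patient with one, although the number was collected. In both cases information is lost that a rank test would use.

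At stake is a missed difference in the number of interventions between the IAH and control groups. The same choice carries over to the ACS and mortality comparisons. Validity is not at stake: the test does not reject too often and does not bias any estimate.

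**Working it through.** **Inputs from the article.** Group sizes come from Sample size calculation: "consisting of 120 controls and 80 patients with IAH". The test level is also there: "two-sided test with an α level of 0.05".

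**The plan's own power figure.** The only one concerns I-FABP (above 90%). With a 0.5 SD difference, power = Φ(0.5 / √(1/120 + 1/80) − 1.96) = Φ(3.464 − 1.96) = Φ(1.504) = 93.4%, so it reproduces at that effect size. It says nothing about interventions.

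**Assumptions, because the article gives no rates.** Counts per patient were drawn from a Poisson distribution, or from a negative binomial with variance m + m²/k, k = 1 or 0.5. Mean counts ran from 0.1 to 2 per patient. There were 24 scenarios with a difference and 9 without, each with 1,500 simulated studies of 120 v 80. Four two-sided tests at 0.05 were applied: chi-squared on every observed value, on 0/1/2/3+, and on any versus none (all uncorrected), and the tie-corrected Mann-Whitney test.

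**Power in selected scenarios, including those that give the smallest and largest losses (%).**

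| Assumed counts (control v IAH mean) | Chi-squared, every value | Chi-squared, 0/1/2/3+ | Chi-squared, any v none | Mann-Whitney |
|---|---|---|---|---|
| Poisson, 0.1 v 0.25 | 62.3 | 62.3 | 69.7 | 69.8 |
| Poisson, 0.2 v 0.4 | 59.7 | 60.3 | 69.8 | 71.6 |
| Poisson, 1.0 v 1.5 | 64.3 | 71.7 | 59.4 | 83.8 |
| Poisson, 1 v 2 | 99.5 | 99.7 | 97.4 | 100 |
| Neg. binomial k=1, 0.5 v 1.0 | 58.1 | 70.9 | 65.5 | 77.9 |
| Neg. binomial k=0.5, 0.1 v 0.25 | 37.8 | 40.1 | 52.0 | 54.6 |
| Neg. binomial k=0.5, 1 v 2 | 33.4 | 54.1 | 45.7 | 66.3 |

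**Range of the loss, Mann-Whitney minus chi-squared, over all 24 scenarios.**

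- Every value its own category: 0.5 points (Poisson 1 v 2, where both tests are near 100%) to 32.9 points (k=0.5, 1 v 2).
- 0/1/2/3+: 0.3 points (Poisson 1 v 2) to 14.5 points (k=0.5, 0.1 v 0.25).
- Any versus none: 0.1 points (Poisson 0.1 v 0.25) to 24.4 points (Poisson 1.0 v 1.5). With a control mean of 0.1 or 0.2 it was 0.1 to 3.7 points.

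Mann-Whitney had the highest power in all 24.

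**Why the last range is so wide.** The loss from any versus none depends on how many patients have repeat interventions. Under a Poisson count, P(2 or more) = 1 − e^(−m)(1 + m). For m = 0.1 and 0.25 this is 0.5% and 2.7%, so almost every count is 0 or 1 and the two tests see nearly the same data. For m = 1.0 and 1.5 it is 26.4% and 44.2%, and dichotomising throws much of the information away.

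**Type I error over the 9 scenarios without a difference.** Mann-Whitney 4.0 to 5.3%; chi-squared on every value 2.1 to 4.4%; on 0/1/2/3+ 3.2 to 5.5%; any versus none 4.1 to 5.6%. No test is materially above 5%. Chi-squared on every value is conservative because of its sparse cells, which is part of its power loss.

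**The case against.** The strongest reply is that the variable may not be a count at all. The treatment-related list speaks of interventions in general, the Table 1 row has no unit, and the example in Study procedures, a decompression laparotomy, reads naturally as something that happened or did not. The article also says that categorical data will be summarised by numbers and frequencies, so the phrase may mean the number of patients with an intervention. Chi-squared is then a standard and valid test. This stands: the per-patient count is the likelier reading of the words, not an explicit one. A reader might infer that chi-squared is wrong for this item on any reading, and the article does not support that.

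A second reply is that interventions may be rare. Background calls decompressive laparotomy the ultimate treatment of ACS, and Sample size calculation cites an ACS prevalence of 4% in a general ICU population. At low rates any versus none loses almost nothing. This also stands for that coding. It does not rescue chi-squared on every value, which lost 7.5 points in the rarest Poisson scenario (69.8 − 62.3).

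A third reply is that a journal article leaves variable coding to the full protocol. That would answer a complaint about missing detail. Here, however, the article itself names the variable, classes it as categorical and assigns the test.

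**Conclusion.** The point holds as a minor one. As worded, the plan classes a number as categorical and gives it a test that ignores order, while a more suitable test stands in the same paragraph. If the variable is a per-patient count, chi-squared was never more powerful than Mann-Whitney in the scenarios examined, and Mann-Whitney kept its type I error near 5%.

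The size of the loss cannot be derived from the article. A reader might be tempted to quote a single narrow figure as the cost of this choice. That is not supported, because the figure moves with the assumed mean, the overdispersion and the grouping. The ranges of about 0 to 33, 0 to 15 and 0 to 24 points are illustrations under the stated assumptions.

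Nor does the choice threaten the study's main conclusions. Outcome measures names I-FABP as primary and Claudin-3 as secondary, the sample size does not rest on interventions, and the mixed model does not use them.

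**What to change.** In Statistical analysis, replace the example. State that the number of secondary interventions per patient will be compared between groups with the Mann-Whitney test. Keep chi-squared for yes/no items, such as the number of patients with any secondary intervention or with a given type. If only occurrence was ever meant, say that the item is the number of patients with an intervention; chi-squared then stays.

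A count model with ICU days as an offset is not recommended as a replacement. It turns the question from a number into a rate, and ICU stay can be cut short by death and may itself differ between the groups.

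The cost is one sentence of analysis wording. If the number is recorded as listed, no new data, patients or procedures are needed.

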### Treatment

Patients with increased pressure determined by the intra-bladder pressure measurements will be treated in compliance with the algorithms for patient management as developed by the WSACS (www.wsacs.org/algorithms.php) [3]. The IAH Assessment Algorithm describes all risk factors that every patient should be screened for upon intensive care unit admission and upon clinical deterioration leading to new organ dysfunction. The intra-bladder pressure will be measured in patients with two or more risk factors for IAH or ACS or in patients who have undergone a liver transplantation. Patients who do not have two or more risk factors at baseline but develop new risk factors during their ICU admission will be followed from that moment onwards. The reason for this is that the occurrence of IAH during intensive care stay is known to be an independent predictor for mortality, whereas presence of IAH at intensive care admission is not [23]. Patients should be enrolled as soon as possible, but at least within 48 hours after meeting the eligibility criteria. The IAH/ACS Management Algorithm provides a decision tree for the follow-up of patients related to the IAP level. The IAH/ACS Medical Management Algorithm provides a stepwise approach of actions to be taken for achieving IAP pressure relief. In short, ICU management will be provided by the attending physicians and may consist of, among others, balanced intravenous fluid administration, correction of hypovolemia, electrolyte disturbances and/or anemia and analgesics.

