The prognostic role of the I-FABP and Claudin-3 on development of IAH, ACS, (increasing) organ dysfunction (based upon SOFA increase) or mortality will be assessed. This analysis will be performed with Stata software, version 10.0 or higher (StatCorp LP, College Station, TX, USA), using the generalized linear latent and mixed model (GLLAMM) framework. Herein, the binary outcome IAH (or new organ dysfuncion or ACS or mortality) will be used as dependent variable, and the level of I-FABP or Claudin-3 will be included in the model as time-dependent variable. Patient ID will be included as clustering variable as up to 13 measurements per patient will be available. Additional covariates such as age, gender, number of IAH risk factors, and BM will be entered into the model in order to evaluate their effect on the relation between biomarker level and outcome. Random intercept and slope will be considered. Results will be expressed as Odds Ratios with their corresponding 95% confidence interval and p-values.

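### The prognostic mixed model does not require the biomarker sample to precede the event, so its odds ratios measure association; mortality needs a once-per-patient or time-to-event model

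*Protocol article*

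**What the plan says.** The last part of Statistical analysis in the Protocol article states its purpose: "The prognostic role of the I-FABP and Claudin-3 on development of IAH, ACS, (increasing) organ dysfunction (based upon SOFA increase) or mortality will be assessed". In the model, "the binary outcome IAH (or new organ dysfuncion or ACS or mortality) will be used as dependent variable". The predictor enters without any condition on its timing: "the level of I-FABP or Claudin-3 will be included in the model as time-dependent variable". The repeated structure is explained by the sampling: "Patient ID will be included as clustering variable as up to 13 measurements per patient will be available". On random effects: "Random intercept and slope will be considered". Results are to be odds ratios with 95% confidence intervals.

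Three other parts of the article bear on timing.
- Under Study procedures, urine and blood are sampled at the same six-hourly time points as IAP. The Table 1 footnote ends follow-up at 72 hours or ICU discharge, not at the event.
- The only working definition of IAH in the analysis section is patient-level and is given for the group comparison: "IAH group; IAP of 12 mmHg or higher on two separate recordings".
- Mortality is recorded over the ICU and hospital stay. SOFA is scored daily, and as a study variable it is the "score on day 1 to 4 (or until ICU discharge or death".

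**The concern.** A prognostic model asks whether a marker measured now tells us who will develop the outcome later. That needs patients who are still free of the outcome and samples taken before it. The text sets neither condition. It gives no lag, no landmark, no end of a patient's rows at the event, and no separate handling of patients with IAH at T0, who can no longer develop it.

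This is the only analysis that the article calls prognostic. The Discussion wants a marker that allows action before damage is irreversible. A marker that rises only once IAH is established could pass this analysis with a convincing odds ratio and still have no value for that purpose.

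Mortality raises a different problem. Death happens once per patient and may fall after the 72-hour window. If it is copied to every row, the outcome does not vary within the cluster, and a random intercept can absorb it entirely.

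**Working it through.** **Inputs from the article:** 200 patients and 80 with IAH, so 80/200 = 40% (Sample size calculation); sampling at T0 and every six hours to T72 (Study procedures). **Assumed:** onset times, size of the post-onset rise, number of deaths and within-patient correlation.

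1. **Rows per patient.** 72/6 + 1 = 13, which reproduces the plan's figure.

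2. **Where samples fall.** Study procedures expects over 95% of pressure-related deterioration within a 12 to 24 hour window. The origin of that clock is not given. If it is enrolment, (72 − 24)/6 = 8 of the 13 scheduled samples (T30 to T72) come after the window.

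3. **IAH simulation** (300 runs, 200 patients, 13 rows each). The biomarker is a patient effect (SD 0.7) plus row noise (SD 0.7), so its total SD is √(0.49 + 0.49) = 0.99. It rises by 1.0, about 1 SD, from onset onwards. Of the patients, 40% develop IAH, with onset uniform over the 13 time points, and IAH persists once present. Before onset the marker carries no information. The fit is logistic regression with patient-clustered standard errors.

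| Outcome on each row | Rows used | Median OR | p<0.05 |
|---|---|---|---|
| Ever IAH | all 13 | 1.65 | 100% |
| IAH at that time | all 13 | 2.83 | 100% |
| IAH in the next 6 h | pre-event only | 1.01 | 4.7% |

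   A separate simulation assumed a smaller rise of 0.5 SD, with half of the IAH present at T0. It gave a same-time OR of 1.56 (p<0.05 in 99% of runs). With the biomarker lagged 6 h in patients still at risk, the OR was 1.00 (6%). Both simulations use population-averaged fits. A random-intercept fit with the 0.5 SD rise also gave a same-time OR well above 1.

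4. **Mortality copied to every row.** With s = +1 for a death and −1 for a survivor, patient i contributes L_i = ∫ ∏_t expit[s_i(a + b·x_it + σu)] φ(u) du. For one simulated cohort (45 deaths in 200, assumed), a and b were maximised at each fixed σ:

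| σ | Log-likelihood | Intercept a | OR = exp(b) |
|---|---|---|---|
| 1 | −621.0 | −1.71 | 1.47 |
| 5 | −194.6 | −4.96 | 1.57 |
| 20 | −126.0 | −16.19 | 1.64 |
| 80 | −111.3 | −61.48 | 1.66 |

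   The likelihood climbs without a maximum towards that of 200 single yes/no outcomes: 45·ln(45/200) + 155·ln(155/200) = −106.6. So σ has no finite maximum-likelihood estimate, although b stays finite. A second check gave the same pattern: −664 at σ = 1 to −137 at σ = 20, with the OR at 1.47 to 1.57.

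5. **Secondary points.** At the cited 4% for a general ICU population, ACS gives 200 × 0.04 = 8 cases. Scaled by 40/32 (an assumption), that is 10. This is few for a model with random effects and several covariates. SOFA is daily against six-hourly biomarkers, and a patient who dies early may have no later score on which to show an increase.

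**The case against.** The strongest reply is that the row-level coding is not stated. IAP is six-hourly and SOFA daily, so IAH and organ dysfunction could be coded by time point, and a condensed article may leave such detail to a fuller document. The patient-level IAH definition belongs to the group comparison. Random effects are only to be considered. The simulated marker was built to rise after onset, so it had to correlate with current IAH. The main aim is also worded as diagnostic, for which a same-time association has some relevance.

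Much of this stands. A once-per-patient outcome is certain only for mortality and is an inference for IAH and ACS. The 99% and 100% figures illustrate a mechanism and are not the plan's error rate. The reply does not remove the core, because both natural codings of IAH admit same-time and post-onset samples, and the stated purpose is prognosis for the development of the outcome.

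Four stronger readings are tempting and are not supported.
- A reader might infer that the mortality odds ratio cannot be computed or swings wildly with software settings. With fine integration it stayed near 1.5. The variance is what diverges, and only if death is repeated on every row and a random intercept is fitted.
- A reader might extend the post-event problem to death, but no sample can follow death.
- A reader might take the Treatment section as proof that IAH at T0 must be separated, since it says that IAH arising during the stay "is known to be an independent predictor for mortality, whereas presence of IAH at intensive care admission is not". That contrast concerns ICU admission and prediction of mortality. T0 is enrolment, which can come later in the stay.
- A reader might call the ACS model overfitted outright. The article expects a higher IAH or ACS percentage than in the general ICU population and fixes no covariate count.

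**Conclusion.** The point holds for what the article fixes. A repeated-row logistic model is called prognostic, but nothing makes the biomarker sample precede the event or removes patients who already have the outcome at T0. For IAH, ACS and organ dysfunction, the odds ratio therefore measures association. Under the assumed effects and onset times, a marker with no prognostic value gave odds ratios of about 1.6 to 2.8, against 1.0 when only earlier samples were used. The sizes depend on those assumptions. An upward bias for a marker that rises after onset does not.

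For mortality the conclusion is conditional. If death is repeated on all rows, a random-intercept model has no finite maximum-likelihood variance, and the odds ratio is conditional on an unbounded patient effect. Coding death in the next interval would avoid this. The SOFA and ACS points are secondary. The primary comparison of I-FABP between the IAH and control groups is not affected.

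**What to change.** In Statistical analysis:
- **IAH, ACS and organ dysfunction:** state the outcome on each row, including whether IAH onset is the first or the second qualifying recording. Include only patients event-free at T0, stop each patient's rows at the event, and use a biomarker value from an earlier interval. For IAH and ACS, a six-hourly discrete-time hazard model with a lagged biomarker would do; for organ dysfunction, the interval should match the daily SOFA score. Report IAH present at T0 separately.
- **Mortality:** use one row per patient at a landmark (for example 24 h, with biomarker values up to then) or a time-to-event model.
- **Secondary:** say how a death before a SOFA increase is handled, and limit or penalise the ACS model if events are few.

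The samples and clinical data are already planned, so the change is wording and programming. The cost is that fewer rows contribute and confidence intervals will be wider. A same-time analysis can be kept if it is labelled as association.

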### Biomarkers released upon loss of small intestinal integrity

Evidence is accumulating that the intestines play a central role in the origin of postoperative and posttraumatic sequelae [4-6]. Enterocyte damage and tight junction loss can be triggered by IAH, and both result in loss of intestinal integrity. As a consequence, toxins, bacteria, and undigested food particles may pass the enterocyte layer, enter the underlying vasculature, and trigger systemic inflammatory reactions that may progress to multiple organ dysfunction syndrome and even death. Peptides released upon enterocyte damage (*e.g.*, Intestinal Fatty Acid Binding protein; I-FABP) or tight junction loss (*e.g.*, Claudin-3) are potentially ideal biomarkers that will help identify patients with early IAH-induced intestinal damage.

I-FABP is a small (14–15 kDa) protein that is exclusively present in mature enterocytes of the small and large intestine. It is released into the circulation upon enterocyte membrane integrity loss and rapidly excreted into the urine (half-life 11 minutes). Elevated I-FABP levels have been found in plasma, serum, and urine in patients with intestinal ischemia, celiac disease, systemic inflammatory response syndrome and necrotizing enterocolitis [7-15]. I-FABP levels can be measured sensitively in plasma, serum, and urine using an enzyme-linked immunosorbent assay (ELISA) [7,8].

Claudins are small (22 kDa) tight junction proteins [4,16-19]. Especially Claudin-3 is expressed in high quantities solely in the intestine [18]. The amount of Claudin-3 in the intestine decreases after tight junction integrity loss [17]. Breakdown of tight junctions by loss of Claudins (as measured on Western blots in urine) is an early event in intestinal damage, resulting in intestinal barrier loss [20].

The main aim of the current study is to investigate if urinary levels of I-FABP can be used as a diagnostic tool for identifying patients at risk for IAP-related complications. Secondary aims are to determine the same for serum levels of I-FABP and for urinary and serum levels of Claudin-3.

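### The prognostic model's single time-dependent biomarker term forces within-patient and between-patient effects to be equal, so its odds ratio can misstate how well the marker tells patients apart

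*Protocol article*

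**What the plan says.** The main aim, given at the end of the Background section on biomarkers, is to find out whether "urinary levels of I-FABP can be used as a diagnostic tool for identifying patients at risk for IAP-related complications". The Discussion repeats it.

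The last paragraph of Statistical analysis describes the prognostic model, a generalized linear latent and mixed model:

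- Outcome: "the binary outcome IAH (or new organ dysfuncion or ACS or mortality) will be used as dependent variable".
- Biomarker: "the level of I-FABP or Claudin-3 will be included in the model as time-dependent variable".
- Clustering: "Patient ID will be included as clustering variable as up to 13 measurements per patient will be available".
- Random effects: "Random intercept and slope will be considered".
- Reporting: "Results will be expressed as Odds Ratios with their corresponding 95% confidence interval and p-values".

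The biomarker term is not split into a patient's usual or baseline level and the movement around it. The text does not say whether the outcome is coded at each time point or once per patient. The paragraph on descriptive analysis defines the IAH group per patient, as "IAP of 12 mmHg or higher on two separate recordings".

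The same section also plans a univariate comparison of biomarker levels between the IAH and control groups (t-test or Mann-Whitney), with similar tests for ACS and death if numbers allow.

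**The concern.** A repeated biomarker carries two kinds of information: some patients run higher than others, and each patient's level moves over time. A single coefficient assumes that both relate to the outcome with the same odds ratio. Where they do not, a random-intercept model returns a weighted average of the two. The random intercept absorbs part of the difference between patients, so the weight can fall mainly on the within-patient part. Allowing a random slope does not separate them.

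The aim is to tell patients apart. A marker that does this well could show a single odds ratio near 1. A marker that only moves together with the event inside a patient could show a large one and be read as identifying patients at risk. Equality of the two effects should not be presumed. The Background gives I-FABP a half-life of 11 minutes, so six-hourly samples can move quickly, and Statistical analysis itself expects a heterogeneous cohort.

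**Working it through.** **The plan's own figures.** Rows per patient: 72/6 + 1 = 13, as stated. IAH patients: 200 × 0.40 = 80, as stated. The stated power above 90% belongs to the two-group comparison, not to the mixed model: with 120 and 80 patients and a 0.5 SD difference, 0.5 × √(120 × 80/200) = 3.46, and Φ(3.46 − 1.96) = 0.934. The article gives no figure for the mixed model, so the rest is simulation.

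**Inputs from the article:** 200 patients, up to 13 rows each, patient as cluster, odds ratio as the effect measure.

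**Assumed inputs, because the article gives none:** outcome coded per time point; marker SD 1; share of marker variance between patients (ICC) 0.3 to 0.85; random-intercept SD 1 to 3; log odds ratio 0.7 per SD (odds ratio about 2.0) for one effect and 0 for the other.

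**Models**, fitted by maximum likelihood with Gauss-Hermite quadrature, 24 data sets per setting:

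- single term: logit p = a + b·x(it) + u(i)
- two terms: logit p = a + bB·x̄(i) + bW·(x(it) − x̄(i)) + u(i)

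Weight of the single coefficient on the within-patient effect: w = (b − bB)/(bW − bB), with the true bB and bW.

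Scenario A is between 2.0, within 1.0. Scenario B is between 1.0, within 2.0. Cells show the single odds ratio and, in brackets, w.

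| ICC | Intercept SD | A | B |
|---|---|---|---|
| 0.3 | 1 | 1.10 (0.87) | 1.80 (0.84) |
| 0.3 | 2 | 1.03 (0.95) | 1.92 (0.93) |
| 0.3 | 3 | 1.03 (0.96) | 1.99 (0.98) |
| 0.5 | 1 | 1.18 (0.77) | 1.72 (0.77) |
| 0.5 | 2 | 1.07 (0.91) | 1.88 (0.90) |
| 0.5 | 3 | 1.04 (0.95) | 1.90 (0.92) |
| 0.7 | 1 | 1.30 (0.63) | 1.44 (0.52) |
| 0.7 | 2 | 1.16 (0.79) | 1.71 (0.77) |
| 0.7 | 3 | 1.10 (0.86) | 1.82 (0.86) |
| 0.85 | 1 | 1.57 (0.35) | 1.32 (0.40) |
| 0.85 | 2 | 1.29 (0.63) | 1.55 (0.63) |
| 0.85 | 3 | 1.25 (0.68) | 1.64 (0.70) |

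Example of w (ICC 0.5, SD 2, scenario B): ln 1.88/0.7 = 0.631/0.7 = 0.90. The weight exceeds 0.5 in 22 of 24 settings. The two exceptions have ICC 0.85 with intercept SD 1.

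In that middle setting the two-term model gave between-patient odds ratios of 1.91 (A) and 1.02 (B). The between-patient effect was significant in 83% of runs under A and in none under B. The single term was significant in 25% (A) and 100% (B). These rates are rough, given 24 data sets and approximate standard errors.

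**Choice of between-patient term** (ICC 0.5, intercept SD 1.5):

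| Term | A (truth 2.0) | B (truth 1.0) |
|---|---|---|
| Single time-dependent level | 1.09 | 1.81 |
| T0 level, with change since T0 | 1.42 | 1.37 |
| Patient mean, with deviation | 1.85 | 1.02 |

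The T0 term was closer to the between-patient truth than the single term at each ICC tried (0.3, 0.5, 0.8). It remains a blend, because one sample holds both the patient's usual level and that moment's deviation.

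**Outcome constant within patient** (as for mortality), copied over 13 rows, 15 data sets per case: the estimated intercept SD averaged 406 (true log odds ratio 0) and 929 (true 0.7). The mixed-model log odds ratios averaged −1.63 and 1.76. Logistic regression with one row per patient gave 0.09 and 0.74.

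**The case against.** **The between-patient question is already tested.** The IAH-versus-control comparison addresses it directly, and the power statement rests on it. This stands and limits the damage: a marker that separates patients would be looked for there. But that comparison is univariate. The mixed model is the only covariate-adjusted prognostic analysis, so its odds ratio is likely to be cited for the risk claim.

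**The leaning towards the within-patient effect is assumed.** This also stands. It needs an outcome coded per time point and depends on an ICC and an intercept variance that the article does not give. The scenarios are deliberately extreme, with one effect exactly null. If the two effects are equal, the single odds ratio does not mislead on this point.

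**Within-patient change is part of the purpose.** The Background wants the marker to inform the timing of decompression, and a rising level bears on that. This is a reason to report both effects, not to merge them.

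**Decomposition is detail that a condensed article may leave to an analysis plan.** That would excuse silence. Here the article states how the biomarker enters the model, and the stated form carries the equality assumption.

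**A further reading concerns the scale.** A reader might add that the conditional odds ratio exaggerates the effect across patients. With log OR/√(1 + 0.346σ²), a conditional 3.0 becomes about 2.3 at σ = 1.5, and 1.8 to 1.4 at latent correlations of 0.7 to 0.9. The size therefore depends on an unstated variance, and a conditional odds ratio is a standard effect measure, not an error.

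**Conclusion.** The point holds in a conditional form. The single term forces the within-patient and between-patient effects to be equal. With an outcome coded per time point and unequal effects, the odds ratio is a blend that can understate or overstate how well the marker tells patients apart. Under the assumed settings the weight on the within-patient effect ranged from 0.35 to 0.98. A true between-patient odds ratio of 2.0 with no within-patient effect appeared as 1.03 to 1.57. No between-patient effect with a within-patient odds ratio of 2.0 appeared as 1.32 to 1.99.

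A reader might infer that the model necessarily reports mainly within-patient change, or that the study cannot answer its aim. The article supports neither. It leaves the outcome coding open and gives no variance components, and it plans a separate between-patient comparison. For an outcome fixed within the patient there is no within-patient contrast. The difficulty there is a model whose intercept variance is not usefully estimable.

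**What to change.** In the prognostic-model paragraph of Statistical analysis:

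1. State for each endpoint whether the outcome is coded per time point or once per patient.
2. For outcomes coded per time point, replace the single biomarker term by the patient's mean level and the deviation from it, and report both odds ratios. Rest statements about which patients are at risk on the mean term, and statements about a rising marker on the deviation term.
3. Also report the T0 level with the change since T0, as the forward-looking version that uses no future samples. Do not describe the T0 term as a pure between-patient effect.
4. For outcomes that occur once per patient, such as mortality, use one row per patient with a level measured before the outcome, such as T0.

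No new data are needed. The cost is wording, an extra model term, and somewhat less precision for each odds ratio than for a pooled one. The patient mean draws on later samples, so it describes differences between patients and is not a prediction available at baseline. Item 3 covers that use.
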